### Data collection methods

#### Evaluations to characterize the elderly participants

##### Fragility assessment

To characterize the elderly regarding fragility we will use the Physical Performance Test scale [24], which classifies the elderly as nonfragile (32 to 36 points), slightly fragile (25 to 31 points) or moderately fragile (17 to 24 points).

This scale scores the performance of nine tasks: 1) raise a book from waist height to a shelf above shoulder level; 2) put on and take off a coat (participants put on and take off an appropriately sized standard apron as quickly as possible); 3) participants retrieve a penny coin that is located in front of the foot as quickly as possible; 4) participants sit, stand fully, and sit back in a chair that has a seat height of 40 cm without using their hands five times as quickly as possible; 5) participants rotate clockwise and counterclockwise quickly, but safely, and are subjectively rated for stability and the ability to produce a rotating motion; 6) walking 15 m by walking 7 m in a straight line, turning, and returning to the initial starting place as quickly as possible and safely; 7) climb 10 flights of stairs one at a time as fast as possible; 8) participants climb four flights of stairs (one point is given for each flight of stairs completed); and 9) participants are scored according to their ability to keep their feet together for 10 s.

The score ranges from 0 to 4 for each task, with a maximum score of 36, being: 0 = impossible to complete; 1 = ends with difficulty, above 10 seconds; 2 = ends with difficulty in 10 seconds; 3 = ends safely over 10 seconds; and 4 = finishes safely in 10 seconds.

This Physical Performance Test scale was adapted into Portuguese by Mitre et al. [24]. The intraclass correlation (ICC) was 0.81 (95% confidence interval (CI) 0.51–0.93) for the reliability of the same examiner, and ICC was 0.86 (95% CI 0.63–0.95) for reliability between different examiners. Cronbach’s α coefficient was 0.89 and 0.92, respectively.

##### Depression scale

The 15-item Geriatric Depression Scale is one of the most widely used assessment tools for assessing depressive symptoms [37]. The questionnaire contains 15 questions that are applied as an interview, with the score sums of each question interpreted as follows: 0 to 5 points, no depression; 6 to 10 points, mild depression, 11 to 15 points, severe depression.

The purpose of this scale is to track the symptoms of depression, requiring medical evaluation for a definitive diagnosis. We will investigate whether the participant’s initial emotional state will affect the outcomes. Participants who have symptoms of depression which persist after the study ends will be referred to a specialist.

All assessments will be performed pretraining, after 24 training sessions and 30 days after the end of 24 sessions (30-day follow-up).

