## Methods

To participate in the study, elderly individuals who have the following eligibility criteria will be recruited from the community.

To be included, participants must be between 60 and 80 years old, sign an informed consent form, be able to independently stand and walk without a care device (i.e., be nonfrail elderly) as classified by the Physical Performance Test scale [24] and be hemodynamically stable (blood pressure <140 and 90 mmHg) according to the guidelines of the Brazilian Society of Cardiology [25].

Exclusion criteria include: experiencing amputation or immobilization of a lower limb; musculoskeletal conditions that would restrict the execution of training; chronic or progressive neurological conditions of central or peripheral origin that cause motor limitations; pain that impedes the execution of training and evaluation; diagnosis of acute coronary syndrome or severe heart condition (score >4 on the New York Heart Association functional classification [25]); presence of chronic obstructive pulmonary disease, asthma, cystic fibrosis, or interstitial lung disease; cognitive impairment with a score less than 26 literate and 13 illiterate in the Mini-Mental State Examination [26]; visual impairment that prevents training; pacemaker use; or any contraindication to the use of tDCS, such as history of seizure or recurrent epilepsy, tumor of the brain, metallic material near the stimulation site, skin infection or injury at the electrode application site.

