### Intervention

#### Multicomponent training

According to the American College of Sports [10], for physical activity to be considered multicomponent training, it must contain at least three components. Components can be activities based on coordination of movement, balance, flexibility, cardiorespiratory capacity, muscle endurance, agility and cognition.

Therefore, our multicomponent training protocol was based on these recommendations, and will be performed in the following sequence: 1) a warm-up period, during which the individual must walk along a straight and flat track of 20 m for 5 min; 2) a cardiorespiratory capacity component where the individual should ride a stationary exercise bike for 20 min; 3) a lower limb strength training component, where the individual should sit and stand up from a chair without support for the upper limbs for 5 min; 4) a balance component, where the individual should walk 10 m along a path that will contain obstacles to deflect them (zigzag in cones) and another 10 m walk on unstable surfaces (carpets of different thickness) and up and down two steps; the individual will perform these components for 10 min; 5) an upper limb strength training, coordination, balance, and cognition component, where the individual should transfer three balls, weighing 1 kg each, from an upper shelf (at shoulder level) to a lower shelf (at pelvis waist level) and then to the floor, and then return the objects to the top shelf in the same sequence for 10 min; and 6) a flexibility and cooling-down component, where the individual will perform stretching in the standing position and relaxation in the sitting position for 5 min.

The sessions will be individualized, lasting 50 min, and in the 20-min period of training on the bike tDCS will be applied.

The Karvonen formula (220 – age) [27] will be used to determine the maximum heart rate of each participant, considering effort on a submaximum test of 60% to 80% of predicted heart rate. Before initiating training, the exercises will be demonstrated to familiarize the participants with the procedures. The treatment will be performed twice a week for 12 weeks (for a total of 24 sessions).

The following variables will be measured before, during (if necessary) and after each multicomponent training session as a protective measure against possible risks: heart rate, respiratory rate, blood pressure, oxygen saturation and lower limb fatigue level [28].

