If the participants have any symptoms or signs that suggest a risk, the training will be stopped immediately. At the treatment site, there is a fire department rescuer who can be called for a medical emergency. All training sessions will be assisted and monitored by an experienced physiotherapist and two physiotherapy students positioned next to the participant.

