## Discussion

The present study will aim to compare the effects of multicomponent training associated with active and sham tDCS on the functional capacity in elderly participants after 24 training sessions and 30 days after the end of training.

This objective was based on research showing that the use of tDCS combined with other therapies has promising effects, as the sum of the two combined techniques can improve cortical activity and motor learning. Fujiyama et al. [43] observed improvements in upper limb motor skills in the elderly with isometric strength training when associated with the simultaneous use of tDCS compared with a control group.

The hypothesis for this study is that after tDCS application, neuronal membrane depolarization will occur, which will facilitate any subsequent therapeutic stimulus, as long-term potentiation is released after anodal tDCS. Therefore, this effect will facilitate motor learning and cognitive training over a long period [44, 45].

These results are important because older people lose their cognitive ability over time, thus justifying the decision to stimulate the area of the lateral dorsal prefrontal cortex which is responsible for the performance of executive functions and for the planning and precise control of complex movement sequences.

Metuki et al. [46] and Hecht et al. [47] report that, by stimulating this area, better actions regarding decisions, memory and movement precision of motor tasks can be observed.

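### The one referral rule printed for depressive symptoms is timed to the end of the study, so a severe-band score at pretraining prompts no printed referral for about 114 days

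*Protocol article*

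**What the plan says.** All of the relevant text on depression is in the protocol article, under Data collection methods, Depression scale.

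- The scale is given as an interview. A score of 0 to 5 counts as no depression; above that the bands are "6 to 10 points, mild depression, 11 to 15 points, severe depression".
- Its status is that of a screen: "The purpose of this scale is to track the symptoms of depression, requiring medical evaluation for a definitive diagnosis".
- The action that follows from a score is given in one sentence: "Participants who have symptoms of depression which persist after the study ends will be referred to a specialist". It does not distinguish between bands or between visits.
- The section closes with the schedule: "All assessments will be performed pretraining, after 24 training sessions and 30 days after the end of 24 sessions (30-day follow-up").

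The Discussion confirms that the follow-up visit belongs to the study, since the effects are to be compared "after 24 training sessions and 30 days after the end of training". The length of training is given under Multicomponent training: "The treatment will be performed twice a week for 12 weeks (for a total of 24 sessions").

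**The concern.** The scale is scored on the first visit, and its top band carries the protocol's own label of severe. The same section says that such a score does not settle a diagnosis and that a doctor has to do so. One would expect the action to be tied to the visit at which the score appears. The printed rule ties it to a later moment, the end of the study, and to symptoms still being present then.

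Participant care is at stake. An older adult with a severe-band score at pretraining could go through the whole course of exercise and stimulation, and further scheduled scoring, before the printed rule calls for any referral. No estimate, test or sample size depends on the point.

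**Working it through.** **Reproducing the plan's own figure.** 2 sessions per week × 12 weeks = 24 sessions, which matches the number stated under Multicomponent training.

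**Time from a pretraining score to the printed referral point.** The article does not define when the study ends, so each reading is shown. Training is assumed to start at about the pretraining visit and to run for exactly 12 weeks.

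| Reading of the study's end | Calculation | Wait |
|---|---|---|
| End of the participant's training | 12 × 7 | 84 days |
| Participant's 30-day follow-up | 84 + 30 | 114 days (114 / 7 = 16.3 weeks) |
| Calendar end of the trial (November 2019, under Trial status), for someone enrolled on the first recruitment day, 21 January 2019 | 21 January to 1 or 30 November 2019 | 284 to 313 days |

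The middle row is the natural reading for an individual, because the follow-up visit is a study assessment. It also fits the article's calendar: a participant recruited on the last planned day, 30 July 2019, would reach day 114 on 21 November 2019, within the month in which completion is expected. On this reading, two scheduled scores (day 0 and about day 84) come before the referral point.

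**Does anything else printed bring referral forward?** The other places that could do so are these:

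- *Eligibility (Methods).* A cognitive score excludes: "cognitive impairment with a score less than 26 literate and 13 illiterate in the Mini-Mental State Examination". No depression score does, so a severe-band scorer can be enrolled.
- *Safety during training (Multicomponent training).* "If the participants have any symptoms or signs that suggest a risk, the training will be stopped immediately". This stops training and is not a referral route for a questionnaire score.
- *Determination of potential side effects.* The questionnaire there concerns brain stimulation.
- *Recruitment.* The weekly calls serve retention.
- *The evaluation sentence in the Depression scale section.* It states a limit of the instrument. It names nobody to act, no score that triggers action and no time.

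None of these supplies an earlier referral for depressive symptoms.

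**Number affected.** The documents do not give the share of participants expected to score 11 to 15, so no number can be derived. Among 28 participants it may be zero.

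**Effect of the proposed change.** Referral at the visit where the score is recorded reduces the wait set by the rule from about 114 days to about 0. If one participant then starts treatment, that is 1 / 14 = 7.1% of an arm.

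**The case against.** The strongest reply is that the sentence gives a sufficient condition, not an exclusive one. It does not contain the word only, and it can be read as a closing duty of care towards those still unwell. A reader might infer that the protocol withholds or forbids earlier referral; the text does not say that. This part of the objection stands, and it limits the point to the timing of the rule that is printed.

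A second reply is that a journal article condenses the full protocol, and that the handling of positive screens may be set out there or in the ethics file. An earlier step may indeed exist. The point survives because it is not about a missing rule: the article prints one, with its timing, and the timing is poor.

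Third, medical evaluation and specialist referral may be separate steps, with evaluation intended promptly. That reading is possible, but the evaluation sentence gives no trigger or time to support it.

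Fourth, a reader might count it as a further harm that someone whose symptoms have resolved by the end is not referred. The documents do not support this as a clear defect: a participant who has fallen to 0 to 5 is in the protocol's own no-depression band.

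Fifth, earlier referral could disturb the trial. The disturbance is limited. The section's stated interest is in the participant's emotional state at the start, and that score is recorded before any referral. Referral on a score also needs no access to the stimulation codes, which one researcher alone holds (Allocation and blindness). A possible co-intervention remains.

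**Conclusion.** The point holds as a cheap improvement for participant safety. The one printed referral rule is set at the wrong moment for a score that the protocol itself calls severe. Followed literally, it leaves such a score at pretraining without referral for about 114 days. That figure assumes that the study ends for a participant at the 30-day follow-up; it is 84 days if the end of training is meant, and longer if the calendar end of the trial is meant. The rule comes late for a pretraining score on all three readings.

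A reader might go further and conclude that severely depressed participants will go untreated in this trial. The documents do not support that. A severe-band score is a screening result and not a diagnosis, no participant is shown to be affected, and an unprinted earlier step cannot be excluded. Nor does the point cast doubt on the sample size or the comparison of functional capacity.

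**What to change.** In the Depression scale section, replace the referral sentence with:

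> A participant scoring 11 to 15 at any visit will be referred for medical evaluation at that visit; other symptoms of depression that persist after the study ends will be referred to a specialist then.

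Add that any treatment for depression started during the trial will be recorded. If the full protocol already contains an earlier step, state it here instead.

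The threshold is the protocol's own severe band. Setting it at 11 is a judgement: scores of 6 to 10 stay under the end-of-study rule.

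The cost is small. The scale is already scheduled at all three visits, so no assessment, visit or eligibility criterion changes. The downside is an occasional co-intervention. Recording it makes it visible but does not remove it.

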#### Assessment of functional capacity

To assess functional capacity, the Glitter-ADL test [31] will be used at three points (pretraining, post-training and 30 days after the end of training). T's an instrument validated for patients with chronic obstructive pulmonary disease, with acceptable reliability (95% CI −0.20 to −0.54).

The Glittre-ADL test is an instrument validated for patients with chronic obstructive pulmonary disease, with acceptable reliability (95% CI −0.20 to −0.54) [31], which has been previously tested in healthy older adults [38, 39], showing excellent intra-rater (ICC 0.90, 95% CI 0.86–0.93) and inter-rater (ICC 0.91, 95% CI 0.88–0.94) reliability (*P* < 0.001 for both). The intra-rater standard measurement error was 0.03 min and the inter-rater standard measurement error was 0.05 min. The minimal detectable change for intra-rater was 0.40 min and for inter-rater was 0.07 min.

The Glittre-ADL test consists of getting up from a chair with a backpack containing one weight (2.5 kg for women and 5.0 kg for men), walking 5 m on a flat track, going up and down steps measuring 17 cm in height and 27 cm in depth, and walking another 5 m to a set of three shelves, one at the top (at shoulder level), one in the middle (at pelvic waist level) and one at floor level. When reaching the shelves, the participant should transfer three balls, weighing 1 kg each, from the top to the middle and then to the bottom shelf and finally from the bottom shelf to the floor, and then return the balls in the same sequence until they reach the upper shelf. The task should be repeated in the reverse sequence until the participant is sitting again.

The complete test consists of five repetitions of this circuit, which should be performed as quickly as possible. Performance is given by the running time (in minutes) of the five laps with a shorter the time indicating better performance, considering a clinically important improvement between 7 and 40 s [38]. To be considered as preserved functional capacity, the test must be performed in approximately 2 min [39].

At the beginning and end of each repeat of the Glittre-ADL test, all of the following measures will be performed for safety monitoring only and will not be used for performance analysis of the Glittre-ADL test as described by Skumlien et al. [31]: blood pressure (measured with a sphygmomanometer; Incoterm model 29,848), heart rate (measured using a Polar FT1 and FT2 monitor), oxygen saturation (measured with a portable digital oximeter) and dyspnea and lower extremity fatigue (using the dyspnea Borg test) [28].

#### Assessment of walking ability

The ability to walk will be assessed by the 6MWT [32], which will be performed at three time points (pre-training, post-training and 30 days after the end of training) in a flat corridor along a 30-m track with markings at each 405 meter.

Participants should walk as fast as possible, without running, while trying to maintain the same pace for 6 min. The participant will be given verbal encouragement every minute using standardized phrases such as “you’re doing well”, “keep up your work”, “you’re halfway there” and “you only have two minutes left” with no expressions or other signs to speed up the pace. If a participant becomes tired, they may slow down or even stop. In the latter case, the timer will not be stopped and the participant will be encouraged to resume the test as soon as they can until the full 6 min are completed.

The test is evaluated by the number of meters traveled during the 6 min, with more meters traveled indicating better test performance.

Heart rate and oxygen saturation will be measured at the third minute of the test. Heart rate, respiratory rate, blood pressure, oxygen saturation and Borg scales [28] for shortness of breath and lower limb fatigue will be assessed at the beginning and end of the test. The 6MWT is a reliable measure that has been validated for the older adult population, with a test–retest reliability of 0.95 [40].

#### Assessment of balance

We will use the mini-BESTest to assess balance [33], which consists of four domains.
Domain 1 (anticipatory postural adjustments) evaluates the participant’s ability to move from a sitting to standing position, stand on tiptoes, and stand on one foot (right then left).Domain 2 (reactive postural responses) evaluates the participant’s ability to perform a protection reaction (during instability) with a step forward, a protective reaction (during instability) with a backward step, and protection reaction (during instability) with a lateral step (right and left).Domain 3 (sensory orientation) evaluates the participant’s ability to stand with their eyes open on a firm surface with feet together, stand with their eyes closed on an unstable surface with feet together, and to stand on a ramp with their eyes closed.Domain 4 (gait stability) evaluates the participant’s ability to change gear while walking, to walk with head movements (rotate the head horizontally), to walk and turn on an axis, to overcome obstacles, and a timed up and go test associated with another task (double-task) by performing a countdown.

The score is given by the performance in the execution of each domain, and each sub-item of the domains is scored as follows: 2 points for normal performance; 1 point for moderate performance; and 0 points for poor performance. The score ranges from 0 to 32 points, with a balance deficit being defined as a score below 24 points.

The participants will perform the tests without shoes. If they are unable to perform any movement independently, minor adjustments or assistance may be made, but their score will be lower. Instructions for each test will be provided in advance so that the participants can perform each test to the best of their ability. Up to three attempts will be allowed and the best result will be considered for analysis. The mini-BESTest is a reliable measure that has been validated for the elderly population, with test–retest reliability (ICC) ranging from 0.50 to 0.82 [33].

#### Assessment of functional independence

The FIM will be used to assess functional independence [34] and will be administered to the participants in interview form to quantify the degree of assistance required during activities of daily living.

This measure has 18 categories grouped into six dimensions for the evaluation of functional and cognitive status: self-care (eating, grooming, bathing, dressing upper body, dressing lower body, toileting), sphincter control (bladder management, bowel management), transfers (bed/chair/wheelchair, toilet, bathtub/shower), locomotion (walk/wheelchair, stairs), communication (comprehension, expression) and social cognition (social interaction, problem solving, memory).

The value attributed to each item ranges from 1 to 7 and is interpreted as follows: 7, completely independent (activity is executed without assistance); 6, modified independence (activity requires special device, care and safety); 5, supervised (individual requires control, support from another person, but with no physical contact); 4, assistance with minimal contact (individual performs >75% of the task without assistance); 3, moderate assistance (individual performs >50% of the task without assistance); 2, maximum assistance (individual performs >25% of the task without assistance); 1, total assistance (individual performs less than 25% of the task without assistance).

The total is calculated from the sum of the FIM dimensions and ranges from 18 to 126 points. The total is divided into four subscores: 18 points, complete dependence; 19 to 60 points, modified dependence (assistance on up to 50% of the task); 61 to 103 points, modified independence (assistance on up to 25% of the task); 104 to 126 points, complete independence. The Brazilian version of the FIM has been validated [34], with high test reliability (ICC = 0.91 to 0.98) and inter-observer reliability (ICC = 0.87 to 0.98).

